## Secondary endpoint (variables)

1. The proportion of women in each group that has negative vaginal cultures for *Candida albicans* at 3 months’ follow-up after prophylactic treatment and at 6 months’ follow-up after the observational phase of the study.
2. Analysis of proportion of women with adverse events (AE) across treatment arms. The AEs will also be reported in descriptive terms and summarized for each treatment arm.
3. Proportion of women with symptom score > 2. Each symptom of typical discharge, itching, dryness of the skin/mucosa, burning and pain will generate 1 point of a composite index (range 0-5).
4. Proportion of women with examination score >2. Each finding of redness skin/mucosa, typical discharge, dry skin/mucosa, fissures skin/mucosa, visible candida hyphae in the microscope will generate 1 point of a composite index (range 0-5).
5. Proportion of women with reduced vaginal lactobacilli content in vaginal smears measured by a semi-quantitative method as normal or reduced quantity.
6. Proportion of women with relapse of *Candida albicans* infection between end of treatment and end of prophylactic treatment (1week post treatment to 3 months’ follow-up) and between 3- and 6 months’ follow-up after end of prophylactic treatment.
7. Proportion of women with possible toxic effect on the vaginal epithelium, defined as disruption and/or inflammation of the epithelial lining, analyzed from vaginal biopsies before and after treatment and prophylaxis.
8. Further analysis of mucosa inflammatory mechanism (histopathology and immunohistochemistry) and biofilm formation during and after treatment and prophylaxis, analyzed from vaginal biopsies. The methods for these *in vitro* exploratory analyses are not yet decided on.

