## Procedures and flow chart

**Five research visits are planned:**

**Visit 1** Screening – oral and written study information, signing of informed consent, vaginal culture for Candida albicans and chlamydia/gonorrhea (PCR test). 45 min.

**Visit 2** Inclusion (baseline), within 1 week after Visit 1. Control for inclusion/exclusion criteria, randomization to study medication after positive culture for *Candida albicans* and negative chlamydia/gonorrhea (PCR test) – health survey, control of concomitant medications, examination, vaginal biopsies, pregnancy test and control of adequate contraceptive methods to avoid pregnancy throughout the study. 1 h.

**Visit 3** 1 week (+2 days) after completed treatment. Control of AE, culture for *Candida albicans* and examination (no biopsies). 30 min.

**Visit 4** After 12 weeks (+ 1 week) from inclusion when prophylactic treatment is completed. Control of AE and relapses, culture for *Candida albicans* and examination, vaginal biopsies. 45 min.

**Visit 5** Follow-up 6 months (+ 1-2 weeks) from baseline/inclusion. Control of AE and relapses, culture for *Candida albicans* and examination (no biopsies). End of study. 30 min.

A weekly web-based dairy (eCRF (Entermedic)) will be used for follow-up of treatment

compliance, efficacy and adverse events. A personal link will be sent via e-mail every week

from week 2-24. During the prophylactic treatment (Visits 2-3) and during the observational

phase of the study (Visit 4-5), the participants are asked to report any suspicious relapses in

the dairy and contact the research midwife if needed. They will also receive equipment for

vaginal cultures that can be used for self-sampling at home to detect true relapses. In case of

positive cultures for *Candida albicans*, they will be offered the same medication as previously

used in the study if the treatment was effective and no adverse events occurred. Otherwise,

an individual treatment option will be used.

Table 1 Flow chart

| **Procedure** | **Visit 1**  Screening  Week -1 | **Visit 2**  Baseline/  inclusion  Week 0  (within 1 w from Visit 1) | **Visit 3**  Follow-up  Week 1  (treatment)  (+2 d) | **Visit 4**  Follow-up  Week 12  (prophylactic phase)  (+1 w) | **Visit 5**  Follow-up  Week 24  (observational phase)  (+2 w) |
| --- | --- | --- | --- | --- | --- |
| Incl/exclusion criteria | √ | √* |  |  |  |
| Informed signed consent | √ |  |  |  |  |

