# Study treatments

## Description of investigational product(s)

The study participants will be randomization to either;

1. **Hibitane®** (investigational treatment), manufactured by Bioglan AB, [name]. 1 ml contains 10 g chlorhexidine gluconate (1%) and 20 mg Cetostearyl alcohol.

Therapeutic indications: anti-septic use for clinical vaginal examinations, especially during delivery.

Administration time: 3 months with additional treatment in case of infection relapse during the observational phase of the study, 3-6 months after inclusion.

Known adverse event: irritation on skin and mucosa.

Restrictions: allergy to the active substance, avoid contact of active substance with brain or meningeal tissue, or ear canal due to neurotoxicity. Hibitane® is approved for vaginal use even during pregnancy and lactation

or

1. **Fluconazole** (control or standard treatment), manufactured by different producers. Oral capsules of 150 mg fluconazol + 139 mg laktos.

Therapeutic indications: different types of fungal infections (cryptocock meningitis, coccidioido mycosis, invasive candidiasis) including mucosal Candia albicans infections.

Administration time: 3 months with additional treatment in case of infection relapse during the observational phase of the study, 3-6 months after inclusion.

Known adverse events: most common side effects are; headache, abdominal pain, nausea, vomiting, diarrhea, skin rashes. For more information, see attached product resume.

Restrictions: allergy to the active substance, doses should be adjusted in case of reduced renal or liver function, concomitant use of medications with known risk of increasing QT-interval and be metabolized via cytocrom P450 (CYP)3A4 (cisaprid, astemizole, pimozid, quinidine and erythromycin). Fluconazole is not approved during pregnancy. For more information, see attached product resume.

Both medication will be prescribed and handled routinely by the pharmacies.

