4. The content of lactobacillus in vaginal wet mount will be analyzed and semi-quantified first at baseline/inclusion and then at 3 follow-ups; 1 week after treatment, 3 months’ follow-up after prophylactic treatment and at 6 months’ follow-up. Routine procedure for wet mount (vaginal secretion with NaCl) will be performed and the amount of lactobacilli will be graded in a light microscope with high magnification (40x and 100x) (Olympus CX41) as either normal quantity (more lactobacilli compared to number of epithelial cell/view field) or reduced (less or absent lactobacilli compared to number of epithelial cell/view field). Differences in proportion of women with normal/reduced quantity between study groups x time will be analyzed. The two investigators will before the study starts, analyzed a number of wet mounts together for inter-rater reliability. All wet mounts will be photo documented via a camera connected to the microscope placed at the department of obstetrics and gynecology, Danderyd Hospital. These photos will be blinded and evaluated by the two investigators together.
5. Data on events of relapses will be collected during the prophylactic and observational phases of the study. The participants will be provided with equipment to collect self-sampled vaginal cultures for *Candida albicans* at home in case of new symptoms of infection. They can also contact the research midwife who could help out with the cultures if needed. Data on relapses will be reported in the CRF.
6. Biopsies from the vaginal mucosa will be used to study possible toxic effect on the vaginal epithelial cells. The biopsies will be taken at baseline/inclusion and at the 3 months’ follow-up and analyzed by histopathology and immunohistochemistry. The biopsies are 3-4 mm, taken by biopsy forceps after local anesthetics. The purpose of the biopsies is to investigate how CHG affect the vaginal mucosa causing possible toxic reactions of the epithelium and impairment of the local immune response. The biopsies will be microscopically examined using ordinary histopathological staining as well as immunohistochemistry for inflammatory and immunological markers. Also PCR analyses for antimicrobial peptides, cytokines, kemokins, cationic intrinsically disordered antimicrobial peptides (CIDAMP) will be performed. Biopsies from participants allocated to FLZ will serve as controls.

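### Culture of a suspected relapse is optional and an uncultured report has no counting rule, so between-visit relapse detection can differ by arm in this open trial

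*Protocol*

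**What the plan says.** Secondary endpoint 6 (Secondary endpoint (variables)) is the "Proportion of women with relapse of *Candida albicans* infection between end of treatment and end of prophylactic treatment", with a second window between the 3-month and 6-month follow-ups. No operational definition of relapse is given.

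Three places describe how relapses are found:

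- **Procedures and flow chart (5.2).** Women are asked to report suspicious relapses in "the dairy and contact the research midwife if needed". They also receive equipment for "vaginal cultures that can be used for self-sampling at home to detect true relapses". Culture is thus what turns a suspected relapse into a true one, but taking it is left to the woman.
- **Methods for secondary endpoints (8.1.2, item 5).** Sampling equipment is supplied for use at home when new symptoms appear, and on the midwife: "They can also contact the research midwife who could help out with the cultures if needed". Relapse data then go into the CRF. Nothing is said about a report that has no culture.
- **Visits 4 and 5 (5.2 and Table 1).** Relapses are reviewed and every woman has a scheduled culture.

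The trial is open. The argument that bias is low (Overall study design, and again under Randomization) rests on the objectivity of the primary culture only. For CHG, section 7.1 states: "Known adverse event: irritation on skin and mucosa". The common side effects it lists for fluconazole (FLZ) are headache, gastrointestinal complaints and skin rash.

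**The concern.** The primary objective covers prophylaxis as well as treatment, but the primary endpoint is read one week after active treatment. The evidence on prophylaxis therefore comes from secondary endpoint 1 (scheduled cultures at 3 and 6 months) and secondary endpoint 6 (relapse). Only endpoint 6 can capture episodes that start and end between visits.

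For those episodes, detection depends on a woman who knows her treatment deciding to swab. The symptom score counts itching, burning and pain, and these are also what local irritation from a cream can feel like. A woman on CHG may put such symptoms down to the cream and not swab. Irritation could equally prompt more swabs on CHG. In both cases the intensity of looking for relapse differs by arm for a reason other than relapse. Randomisation does not protect against this, because the behaviour follows from knowing the allocation. Less swabbing on CHG could hide a real deficit in prophylaxis, and more could create a false one.

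**Working it through.** **The plan's own figures.** The protocol gives no relapse rate and no expected swab uptake, so there is no stated figure to reproduce on this point. Its sample size (23 per group) concerns the primary endpoint and neither supports nor refutes the concern.

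**Inputs from the protocol.** 30 women per arm. Scheduled cultures at weeks 1, 12 and 24, so gaps of 11 and 12 weeks.

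**Assumed inputs (illustrations only).** True symptomatic relapse *p* of 30%, 40% or 50%. Probability *s* that a relapsing woman swabs: 90% v 75% (gap 15 points), or 90% v 60% and 80% v 50% (gap 30 points). Every swab of a true relapse is positive.

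**Step 1: upper end.** Suppose that only swab-positive episodes count and that scheduled cultures catch none of the others. Then observed relapse = *p* × *s*, and with equal true relapse the false difference = *p* × (gap in *s*).

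| True relapse, both arms | Gap 15 points | Gap 30 points |
|---|---|---|
| 30% | 0.30 × 0.15 = 4.5 points | 0.30 × 0.30 = 9 points |
| 40% | 0.40 × 0.15 = 6 points | 0.40 × 0.30 = 12 points |
| 50% | 0.50 × 0.15 = 7.5 points | 0.50 × 0.30 = 15 points |

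For example, at 40% with uptake 90% on FLZ and 60% on CHG, observed relapse is 0.40 × 0.90 = 36% v 0.40 × 0.60 = 24%, or 10.8 v 7.2 women of 30. If the uptakes are swapped, the sign reverses.

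**Step 2: a true difference.** Let true relapse be 45% on CHG and 30% on FLZ, a difference of 15 points.

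- Uptake 60% CHG, 90% FLZ: 0.45 × 0.60 = 27% v 0.30 × 0.90 = 27%. The difference vanishes.
- Uptake 90% CHG, 60% FLZ: 0.45 × 0.90 = 40.5% v 0.30 × 0.60 = 18%. The difference grows to 22.5 points.

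**Step 3: allow for Visits 4 and 5.** Let the scheduled cultures catch a share *c* of unswabbed relapses. Observed relapse = *p* × [*s* + (1 − *s*) × *c*], and the false difference becomes *p* × (gap) × (1 − *c*). With *c* = 50% (an assumption), the 40% example becomes 0.40 × (0.90 + 0.05) = 38% v 0.40 × (0.60 + 0.20) = 32%. The artefact falls from 12 to 6 points. With *c* = 100% it is zero.

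**Step 4: other ways of counting an uncultured report.** The protocol leaves three readings open, and none removes the problem.

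- *As no relapse:* Steps 1 to 3 apply.
- *As relapse:* irritation from the cream would be counted as failure of CHG.
- *As missing:* the amount missing would depend on arm.

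**The case against.** The strongest reply has five parts.

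1. **No counting rule is stated.** A reader might infer from the contrast between suspicious and true relapses that a report without a swab counts as no relapse. The protocol does not say so. Counting it as a relapse or as missing is equally open, and the rule may stand in the SAP, which is not shown. This is right, so the figures in Steps 1 to 3 hold under one reading only. An SAP can classify a report, but it cannot recover a swab that was never taken, and the trigger for sampling is a protocol procedure.
2. **Sampling is less optional than it looks.** Section 8.1.2 links the kit to new symptoms, and the offer of repeat study medication follows a positive culture, so women in both arms have a reason to swab. This makes low uptake less likely. It does not make swabbing a requirement or equal between arms.
3. **Scheduled cultures limit the damage.** Both relapse windows close on a visit where everyone is cultured, so an untreated infection may still be found. A reader might conclude that the comparison rests entirely on who swabs, and the protocol does not support that. What remains exposed is the episode that clears or is treated in between.
4. **The irritation mechanism applies mainly while CHG is in use.** In the 3-to-6-month window it is used only as retreatment. This stands: the first window is the more exposed.
5. **A rule triggered by suspected relapse would miss its target.** A woman who blames the cream will not report a relapse either. This also stands, and it decides the form of the fix.

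**Conclusion.** The point holds in a limited form. Culture of a suspected relapse is worded as optional, the protocol does not say how an uncultured report counts, and its low-bias argument does not extend to swabs that the woman initiates. Between-visit ascertainment of secondary endpoint 6 can therefore differ by arm, chiefly for episodes that clear or are treated before Visits 4 and 5.

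Direction and size cannot be derived from the document. The 4.5 to 15 points are an upper end. They assume true relapse of 30% to 50%, uptake gaps of 15 to 30 points, that only swab-positive episodes count, and that no scheduled culture catches the rest. They shrink in proportion to what Visits 4 and 5 catch. A reader might take the overlap with irritation to mean that the bias favours CHG, but the opposite is just as compatible with the text.

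Only a secondary endpoint is affected. The primary endpoint and secondary endpoint 1 use scheduled cultures from all women. The change is still worth making before recruitment, because the lost samples cannot be replaced afterwards.

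**What to change.** - **Sampling rule (5.2 and 8.1.2 item 5).** Replace the permissive wording with a rule for both arms: any new symptom of vulvovaginal candidiasis entered in the weekly diary, whatever the woman thinks caused it, and any reported suspected relapse, prompts a self-sampled culture with the kit already supplied. The diary already collects these symptoms (section 14.1), so the prompt can be attached to that entry.
- **Recording.** Keep symptoms without a culture as a separate CRF category.
- **Reporting.** Give symptomatic episodes and swabs per woman by arm, so that any difference in sampling is visible.
- **Analysis.** Analyse relapse twice, with uncultured episodes counted first as non-relapse and then as relapse. Present the two as bounds. The second should not stand alone, because it would count irritation from CHG as failure.

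The cost is protocol and diary wording and some extra cultures. No extra visit is needed and treatment rules are untouched. If every symptomatic episode is cultured with equal sensitivity in both arms, the artificial difference from unequal swabbing is zero. Symptoms never entered in the diary remain outside the rule.

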| Medical health questionnaire/ concomitant medications |  | √ |  |  |  |
| Randomization |  | √ |  |  |  |
| Vaginal culture  Candida | √ |  | √ | √ | √ |
| PCR test**  Clamydia/  Gonorrhea | √ |  |  |  |  |
| Pregnancy test |  | √ | √ |  |  |
| Symptom score |  | √ | √ | √ | √ |
| Examination score |  | √ | √ | √ | √ |
| Microscopy  lactobacilli |  | √ | √ | √ | √ |
| Vaginal biopsies |  | √ |  | √ |  |
| Instructions for handling the investigational product(s) |  | √ |  |  |  |
| Adverse Events (AE & SAE) |  |  | √ | √ | √ |
| Study end |  |  |  |  | √ |

**if positive culture for Candida albicans*** Chlamydia/gonorrhea test will be repeated in case of new partner during the study

##

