# Subject selection

## Inclusion criteria

To be included in the study, subjects must meet the following criteria:

- 18-50 years of age
- A history of > 2 candida infections the last year
- Symptoms of acute vulvovaginal candida infection
- Culture verified infection with *Candida albicans*
- Adequate contraceptive method
- Able to understand oral and written information in Swedish
- The subject has given written consent to participate in the study

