## Exclusion criteria

Subjects must not be included in the study if any of the following criteria are met:

- Severe somatic or mental illness (including liver and kidney failure and cardiac disease)
- Immunosuppressive medication
- Pregnancy
- Lactation
- Other ongoing gynecological infections
- Allergy to fluconazole or chlorhexidine gluconate
- Citalopram or other medication that might have impact on the QT interval (terfenadin, cisaprid, astemizol, pimozid, kinidin, erythromycin, halofantrin, amiodaron)
- Participation or recent participation (30 days) in a clinical study with an investigational product. Previous participation in this study.

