## Dose and administration

1. Hibitane® is a cream and will be applied vaginally by the help of a 10 ml plastic syringe (Braun, Melsungen, Germany, CE 0123), provided to the participants randomized to Hibitane®. During the first week of treatment 8 ml is used every night at bedtime and thereafter 8 ml will be used at night once a week for 11 consecutive weeks. The dose of 8 ml is considered an adequate to be applied in the vagina for achieving treatment effect. Most of the cream will stay in place, but a small portion will leak and a genital pad is recommended. Dose changes or withdrawal of the medication will be considered in case of AE.
2. Fluconzole® oral 150 mg capsules will be used every 3 days for the first 3 doses, thereafter as prophylactic treatment with 150 mg/week for another 11 consecutive weeks. The fluconazole regime serves as the reference medication normally used for recurrent vulvovaginal candidiasis according to international recommendations and FASS. Fluconazole can be taken regardless of food intake. Dose changes or withdrawal of the medication will be considered in case of AE.

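### The relapse rule lets fluconazole be restarted in months 3–6 with no condition on current medication, contraception or pregnancy, and the QT-drug ban has no scheduled check after Visit 2

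*Protocol*

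**What the plan says.** **Re-treatment.** The text on relapses in the protocol's section 5.2 (Procedures and flow chart) lets women with a positive culture have the same medication again, if it was "used in the study if the treatment was effective and no adverse events occurred". Otherwise an individual option is chosen. Section 7.1 (Description of investigational product(s)) gives the administration time in both arms as three months, with "additional treatment in case of infection relapse during the observational phase of the study, 3-6 months after inclusion". Section 7.3 prescribes 18 fluconazole capsules and accepts that more may be needed at relapse. Section 7.8 (Concomitant medications) adds a rescue rule for both arms: a positive culture with symptoms, called treatment failure, leads to vaginal clotrimazole for the rest of the study.

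**Pregnancy and contraception.** Section 7.1 states: "Fluconazole is not approved during pregnancy". "Adequate contraceptive method" is an inclusion criterion. The Visit 2 entry in section 5.2 lists "control of concomitant medications, examination, vaginal biopsies, pregnancy test and control of adequate contraceptive methods to avoid pregnancy throughout the study". Table 1 ticks a pregnancy test at Visits 2 and 3, and section 9.6 says that the test is done twice, before active and before prophylactic treatment.

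**Other medicines.** The exclusion criteria bar "Citalopram or other medication that might have impact on the QT interval". Section 7.8 keeps drugs named there barred after inclusion and says that concomitant medications are reported in the CRF. In Table 1 the row "Medical health questionnaire/ concomitant medications" carries one tick, at Visit 2. After the three initial doses, fluconazole is taken "thereafter as prophylactic treatment with 150 mg/week for another 11 consecutive weeks" (section 7.2).

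**The concern.** Section 9.6 ties a pregnancy test to each planned start of treatment, but the restart at relapse, which the protocol also plans, has none. The relapse rule looks back, at whether the drug worked and was tolerated. It does not ask whether the woman may still take it: whether she has since started an interacting drug, stopped contraception or become pregnant. At stake is an avoidable exposure to fluconazole in early pregnancy or alongside a QT-affecting drug. The background section names QT prolongation and arrhythmia as the most serious interaction. It also says that interacting drugs, among them several antidepressants, are common in these patients.

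The second, lesser concern is that the benefit-risk section and section 11.1 lean on the entry criteria to contain the fluconazole risk. The ban on QT-affecting drugs continues through the study, but the schedule names no visit after Visit 2 at which it is checked.

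**Working it through.** The plan gives no figure on this point, so there is none to reproduce. The check sets the schedule beside the re-treatment rule and counts weeks. All weeks are nominal, without the visit windows.

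**Inputs**
- Re-treatment window: 3–6 months after inclusion (section 7.1), that is, weeks 12 to 24 on the scale of Table 1.
- Last scheduled medication and contraception control: Visit 2, week 0 (section 5.2, visit list; Table 1 for medication).
- Last scheduled pregnancy test: Visit 3 (Table 1; section 9.6). Table 1 puts Visit 3 at week 1. The visit list puts it one week after completed treatment, which is about week 2 after a one-week active course.
- Fluconazole regimen: 3 initial doses, then 11 weekly doses (section 7.2). Capsules prescribed: 18 (section 7.3).

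**Gap = week of restart − week of last scheduled check**

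| Last check | Week | Restart at week 12 | Restart at week 24 |
|---|---|---|---|
| Medication and contraception (Visit 2) | 0 | 12 − 0 = 12 | 24 − 0 = 24 |
| Pregnancy test (Visit 3, Table 1) | 1 | 12 − 1 = 11 | 24 − 1 = 23 |
| Pregnancy test (Visit 3, visit list) | 2 | 12 − 2 = 10 | 24 − 2 = 22 |

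The gap is 12–24 weeks for medication and contraception. For pregnancy, over both readings of Visit 3, it is about 10–23 weeks.

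**Would a new prescription force a check?** Not necessarily. The regimen uses 3 + 11 = 14 capsules, and 18 − 14 = 4 remain. The relapse rule states no dose. If re-treatment repeats the three-dose course (an assumption), it can be taken from the remaining capsules. Relapse cultures can be self-sampled at home, so a visit is not guaranteed either.

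**Does the clotrimazole rule close the gap?** It applies to treatment failure, defined by a positive culture and symptoms. The relapse rule in section 5.2 asks for a positive culture and allows the same drug again. Sections 7.1 and 7.3 both expect further study drug at relapse. Read together, the clotrimazole rule reduces the number re-treated with fluconazole but cannot bring it to zero without cancelling the other three statements.

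**Medication check during dosing.** Scheduled checks at Visits 3, 4 and 5: 0 of 3. The visit list agrees with Table 1. All 11 weekly doses come after the only scheduled check, and no visit is planned between Visit 3 and Visit 4 at week 12.

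**Effect on the primary analysis.** The primary culture is taken at Visit 3, before the re-treatment window opens. The sample size rests on 86% success in each arm and a 30% margin, and neither depends on these checks.

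**The case against.** The strongest reply concerns the medication check, and much of it stands. Table 1 is not a complete list of what is done: section 7.4 has compliance evaluated at the follow-up visits, yet compliance has no row. The single tick sits on a row shared with a questionnaire that is filled out only at inclusion. Section 7.8 continues the ban and requires medicines to be reported in the CRF, and section 14.1 provides a paper CRF for all five visits. Grading an adverse event under section 9.2.1 means considering other medications, and adverse events are asked about at Visits 3, 4 and 5.

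A reader might infer that other medicines go unrecorded during treatment, or that entry screening is the only safeguard against QT interactions. The documents do not support either reading. What remains is narrower: there is a duty to record but no scheduled question, and a drug started without causing a new symptom need not come to light through adverse-event reporting. The two descriptions of the weekly diary do not mention medicines, but neither claims to be a full item list.

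On re-treatment, it can be said that the drug is offered, so a clinician decides. The window also opens around a face-to-face visit, contraception is controlled at Visit 2 with the whole study in view, and the restrictions in section 7.1 apply whenever fluconazole is prescribed. These points lower the likelihood of harm. They do not supply the missing condition, because a relapse can occur at any time up to week 24 and the only stated tests are prior effect and absence of adverse events.

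**Conclusion.** The main point holds. The stated rules allow fluconazole to be restarted about 10–23 weeks after the last scheduled pregnancy test, and 12–24 weeks after the last scheduled medication and contraception control, with none of the three required at restart. The secondary point holds in limited form: the QT-drug ban continues and medicines are to be reported, but no verification is scheduled during the 11 weekly doses.

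The week counts assume nominal visit times and re-treatment within months 3–6. The documents give no rate of relapse, pregnancy or new QT-drug use, so the number of women affected cannot be calculated; the clotrimazole rule reduces it by an unknown amount. The concern is confined to the fluconazole arm (30 women planned), since section 7.1 describes Hibitane as approved for vaginal use in pregnancy. It is a matter of patient safety, with no effect on the primary endpoint, power or error rates. Visit schedules and re-treatment conditions belong in the protocol, so this is not something to leave to the statistical analysis plan. The sponsor should make the change.

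**What to change.** 1. Add to the relapse rule in section 5.2: *Before any re-treatment with fluconazole, current medication is checked against the exclusion list, contraception is confirmed and a urine pregnancy test is negative.* Amend the statement in section 9.6 that the test is done twice so that it includes this third occasion.
2. Tick concomitant medications at Visits 3, 4 and 5 in Table 1, in line with section 7.8.
3. Optional: one weekly diary item asking about new medicines, passed to the investigator when positive. It would cover the weeks between Visits 3 and 4.

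The cost is slightly more data entry and a urine test for women re-treated with fluconazole. No new visit or staff is needed.
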